## **1 INTRODUCTION**

### **1.1 Clinical Experience and Research Hypothesis**

Various phase II clinical studies using ipilimumab in stage IV have been conducted. Results of the first pivotal phase III study MDX010-20 have been presented at ASCO 2010 (O'Day et al., JCO; 2010) and are published in NEJM (Hodi et al., NEJM, 2010). In the second ongoing phase III trial CA184-024, a different dose and treatment scheme is currently tested. Results are expected at the end of 2010.

However, due to strictly defined inclusion and exclusion criteria in phase III trials, results of registrational trials might not answer all questions regarding safety and efficacy of ipilimumab in all advanced melanoma patient cohorts seen in daily routine. E.g. on one hand, in MDX010-20 trial, only patients positive for HLA-A2 could be enrolled (since patients were randomized in a double-blind fashion in a 1:3:1 ratio to receive HLA2-restricted melanoma gp 100 peptide vaccine monotherapy, MDX-010 in combination with melanoma gp100 peptide vaccine, or MDX-010 monotherapy.) In the second currently ongoing phase III study CA184-024 patients were not restricted to HLA-A2+ haplotype. However, another dosing and treatment scheme was tested (combination with DTIC; ipilimumab 10mg/kg and maintenance period following induction phase for patients who benefitted from ipilimumab) Moreover, only previously untreated patients could be enrolled. Patients with primary mucosal melanoma were excluded in CA184-024 study; patients with primary ocular melanoma were excluded in both MDX-010-20 as well as in CA184-024.

The currently described study concept with ipilimumab 3mg/kg would make a rational therapeutic strategy in a broad range of pretreated metastatic melanoma patients seen in daily clinical practice promising an efficacious and safe strategy in the therapy of the advanced stage malignant melanoma.

### **1.2 Product Development Rationale**

A large clinical phase II is proposed to treat a broad range of metastatic melanoma patients who have failed or did not tolerate at least one prior systemic treatment in metastatic or non-resectable stage III disease in order to gain more information about and further characterize efficacy and safety of ipilimumab in a broad range of clinically relevant patient cohorts seen in daily routine, neither addressed in MDX-010-20 study nor in CA184-024. Enrollment will not be restricted to any specific HLA subtype and patients with uveal or ocular melanoma can be treated with ipilimumab as well. Furthermore patients with brain metastases and documented control for at least 3 months will be eligible. Potential predictive markers (ALC, b-raf mutation

status) will be prospectively evaluated. Wide access to ipilimumab in skin cancer-specialized clinical centers will be achieved in addition to a standardized evaluation of its clinical results and currently employed algorithms so cope with occurring adverse events. Patients will be treated according the MDX-010-20 protocol with ipilimumab monotherapy 3mg/kg four times during the induction phase only. Patients who benefit from therapy (stable disease of  $\geq 3$  months beginning at Week 12 or patients with initial partial or complete response at Week 12 assessment) and did not show any immune-related adverse event (irAE)  $\geq$  grade 3 will be eligible for treatment re-induction in the case of melanoma relapse. RE-induction will be part of the study if relapse occurs during 12 months after first receipt of study medication. Re-induction will not be part of the protocol if relapse is experienced after individual end of trial (12 months post first receipt of study medication)

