**Secondary Endpoint (s)**

- All adverse events  $\geq$  Grade 3 according to CTCAE, Version 4.0 criteria, that are definitely, probably, or possibly related to the administration of the investigational agents will be assessed.
- Overall response rate (PR+CR) according to immune-related response Criteria (ir-RC) at any time in the study.
- Disease control rate irDCR (rate of CR or PR or SD) according to immune-related response Criteria (ir-RC) at any time in the study.
- Overall response rate (PR+CR) according to RECIST criteria at any time in the study.
- Disease control rate (CR or PR or SD) according to RECIST criteria at any time in the study.
- Progression free survival rate at 6 months, PFS is defined as the time from the first study treatment date until the first documented tumor progression date (as defined by immune related response criteria) or date of death, whichever occurs first.
- Overall survival
- Clinical efficacy parameter (1-year OS, ORR, DCR, PFS at 6 months) according to b-raf mutational status of tumor (b-raf V600E yes versus no), brain metastases, LDH and HLA-A2

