| Clinical Drug Supplies                                                     |                                 |                                                                                                                                              |                                                                 |                                                               |                                           |                            |
| Dispense Study Treatment                                                          |                                 | X                                                                                                                                            |                                                                 |                                                               |                                           | 5.                         |
| Survival assessment                                                               |                                 | X                                                                                                                                            | X                                                               | X                                                             | X                                         | 6.1.1.5                    |
| Translational Research Programm
(separate informed consent)            |                                 |                                                                                                                                              |                                                                 |                                                               |                                           |                            |
| Whole venous blood 20ml                                                           | X                               |                                                                                                                                              | X n                                                  |                                                               |                                           | 6.4                        |

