| EDTA "full blood" 2 ml                                                            | X i                  |                                                                                                                                              |                                                                 |                                                               |                                           | 6.4                        |
| Tissue biopsy (an additional fresh biopsy is optional)                            | X j                  |                                                                                                                                              |                                                                 |                                                               |                                           | 6.4                        |

a/b Includes visits during induction and re-induction periods of the study.

c Blood pressure every 30 minutes during ipilimumab + 1 hour following completion of infusion (Sect. 6.2.1.2)

d All period laboratory samples must be collected within a window of up to 3 days before administration of ipilimumab

e TSH, free T4 at baseline, Visit 2, 3, 4, 5. **The assessment of TSH at baseline and before each treatment is mandatory. The TSH level must be available to the investigator prior to each administration.**

f A pregnancy test must be conducted and a negative result must be confirmed before the first administration of ipilimumab and after week 12

g within 6 weeks before start of therapy.

h The same method of assessment must be used throughout the trial to ensure comparability

i EDTA "full blood" for SNP, HLA-A2 typing once at the beginning of the study or any other time point of the study

j if not available until then, for b-raf status of tumor biopsy

k laboratory parameters: evaluation for LDH and S-100 should be performed at baseline, visit 2,3,5 (week 4, 7, 12)

l at baseline and week 12, if clinically indicated (evident of myocarditis e.g. dyspnoea, functional insufficiency) to be done before each treatment

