### 2.2 Secondary Objectives

To explore safety and additional efficacy parameters of the ipilimumab treatment in certain subgroups: (cutaneous versus uveal versus mucosal melanoma; LDH < 2 ULN versus LDH ≥ 2 ULN; status brain metastases versus no brain metastases in medical history; b-raf mutation positive versus b-raf mutation negative)

Secondary objectives are

- Safety / toxicity according to the CTC Criteria (Version 4.0)
- Efficacy according to immune-related response criteria (ir-RC) at any time during treatment
- Efficacy according RECIST criteria
- Progression free survival rate at 6 months
- Overall survival
- To explore clinical efficacy of ipilimumab in relation to b-raf mutation status, brain metastases and LDH

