#### 9.5. Statistical analysis

The primary endpoint, one year survival rate, is based on the ITT population. As a simple rate, it will be calculated as the number of patients being still alive 12 months after their first administration of the study treatment divided by the number of patients having received at least one administration of the study treatment. Only subjects known to be alive at 1 year will be included in the numerator. As a time to event variable, it will be derived from the Kaplan-Meier curve. In this case missing data will be censored at the last contact. See below for further details.

All other analyses will have exploratory character. Results will be presented overall and per cohort/subgroup:

- (1) cutaneous vs uveal vs. mucosal melanoma
- (2) - LDH < 2 UNL versus LDH ≥ 2 UNL
- (3) - status brain mets versus no brain mets in medical history
- (4) - status Braf mutation positive versus. Braf mutation negative
- (5) - HLA-A2 positive versus HLA-A2 negative

Demographic and baseline characteristics will be tabulated for all treated subjects. For categorical variables, summary tabulations of the number and percentage within each category (with a category for missing data) of the parameter will be presented. For continuous variables, the mean, median, standard deviation, minimum and maximum values will be given.

Proportions (Survival rate at 1 year, irOR, irDCR, irPFS at 6 mths, OR and DCR) will be presented with exact (Clopper and Pearson) two-sided 95% CI. irOR, irDCR and irPFS are defined according to the irRC; OR and DCR according to RECIST; The date of origin for the survival rate at one year, and irPFS at 6 months is the date of the first ipilimumab dose. Only subjects known to be progression free at 6 months / alive at 1 year will be included in the respective numerators. Any subject receiving at least one dose of ipilimumab will be included in the denominators. The denominator for the irOS and irPFS analyses will be the ITT population. The denominator for the irOR, and irDCR, OR and DCR will be the Response-evaluable population..

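### HLA-A2 typing rests on a tube drawn only under a separate consent and possibly late, so 1-year survival by HLA-A2 may come from a selected subset

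*Protocol*

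**What the plan says.** **Why HLA-A2 appears.** Section 1.1 notes that in the pivotal phase III study "only patients positive for HLA-A2 could be enrolled". Section 1.2 answers that here "Enrollment will not be restricted to any specific HLA subtype".

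**Planned use.** The synopsis lists HLA-A2 positive versus negative in its secondary objective. Its secondary endpoints ask for 1-year OS, ORR, DCR and 6-month PFS by b-raf status, "brain metastases, LDH and HLA-A2". Section 9.5 says results will be presented by subgroup, and item (5) is "HLA-A2 positive versus HLA-A2 negative". The statistics part of the synopsis says only that such results may be presented. Section 2.2 explores efficacy "in relation to b-raf mutation status, brain metastases and LDH" and leaves HLA-A2 out. The secondary endpoints in 9.3.2 contain no marker-based item at all.

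**Where the status comes from.** In the Time and Events Schedule the 2 ml EDTA tube stands in the translational block, whose heading carries the words "separate informed consent". It is marked in the screening column. Footnote i explains that the tube is "for SNP, HLA-A2 typing once at the beginning of the study", and then allows any other time during the study as an alternative. Section 6.5.1, part of what section 6.5 calls side studies, repeats this. HLA typing is not in the eligibility criteria (4.1, 4.2), the screening tests (6.1.1.1) or the laboratory lists for later visits (6.1.1.2 to 6.1.1.4).

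**The concern.** Four characteristics define the marker-based secondary endpoint in the synopsis. LDH is a routine screening test, brain metastases are known from history and baseline imaging, and the b-raf biopsy has its own row under eligibility assessments. HLA-A2 is the only one obtained solely under a second consent.

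Patients can therefore lack an HLA-A2 status in two ways:

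- **Consent.** A treated patient who does not join the translational programme gives no tube. If those who join are fitter than those who do not, survival among typed patients is too high.
- **Timing.** Survival is counted from the first ipilimumab dose, but the tube may come later. A patient who dies before a late draw is never typed. This pushes survival among typed patients upward whatever one believes about who consents.

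What is at stake is the level of 1-year survival reported for HLA-A2-positive and HLA-A2-negative patients, and some precision. A statistical analysis plan can describe missing status but cannot recover a sample that was never drawn. Consent scope and sampling time are fixed in the protocol.

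**Working it through.** **Inputs from the protocol.** N = 200; 1-year survival 45.6%, rounded to 0.5 for precision (synopsis, sample size); exact Clopper-Pearson 95% intervals (synopsis, statistics; section 9.5). **Not given, so assumed over a range:** uptake of the separate consent, HLA-A2 frequency, the survival gap between typed and untyped patients, and the share of late draws.

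**1. The plan's own precision.** Clopper-Pearson limits are the 2.5% quantile of Beta(x, n−x+1) and the 97.5% quantile of Beta(x+1, n−x). With n = 200 and x = 100 they are 0.429 and 0.571, a width of 14.3 points. This agrees with the stated 0.43 to 0.57. No precision is stated for the HLA groups.

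**2. Consent route.** Let c be uptake, S overall survival, T survival in typed patients and T − d survival in untyped patients. Then S = cT + (1−c)(T−d), so T = S + (1−c)d. The widths are for an HLA group making up half of the typed patients, at p = 0.5.

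| Uptake c | Typed of 200 | Group n | 95% CI width (points) | T if d = 10 points | T if d = 20 points |
|---|---|---|---|---|---|
| 100% | 200 | 100 | 20.3 | 45.6% | 45.6% |
| 90% | 180 | 90 | 21.5 | 46.6% | 47.6% |
| 80% | 160 | 80 | 22.8 | 47.6% | 49.6% |
| 70% | 140 | 70 | 24.4 | 48.6% | 51.6% |
| 60% | 120 | 60 | 26.4 | 49.6% | 53.6% |

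If c and d are the same in both HLA groups, each rises by (1−c)d and the difference between them does not change.

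**3. Timing route.** Under exponential survival, the probability of being alive at week t is 0.456^(t/52). One-year survival from first dose, given alive at a draw in week t, is 0.456^(1−t/52):

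- week 6: 0.456^(46/52) = 49.9%
- week 12: 0.456^(40/52) = 54.7%
- week 24: 0.456^(28/52) = 65.5%

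These apply to patients actually sampled at those times. For the whole typed group, suppose a share f is due for a draw at week 12 and the rest are drawn at baseline. By week 12, 1 − 0.456^(12/52) = 16.6% of the late-draw patients have died untyped, so typed survival is 0.456 / (1 − 0.166f). This gives 46.4% for f = 10%, 47.6% for f = 25% and 54.7% for f = 100%.

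**The case against.** Five points can be made in defence.

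- **Separate need not mean optional.** Section 13.4 takes a consent of its own even for data transfer. Section 6.5.1 speaks of sera from all patients and says the EDTA blood will be collected. Only fresh tissue is labelled optional, and the consent forms are not available here. However, no section makes the translational consent a condition of entry, so a treated patient without HLA-A2 status remains possible. Near-complete uptake is also possible, and selection by consent would then be small.
- **The analysis carries little weight.** Section 9.5 calls everything beyond the primary endpoint exploratory, and the synopsis leaves presentation of these subgroups open. This stands and limits the importance of the point.
- **HLA-A2 is not a main question.** A reader might infer from the rationale that survival in HLA-A2-negative patients is what the trial is for. The documents do not go that far. Sections 1.2 and 1.5 name ALC and b-raf as the potential predictive markers for prospective evaluation. The answer they give to the earlier HLA restriction is unrestricted enrolment, which needs no typing.
- **The contrast may be sound.** An equal shift in both groups leaves positive versus negative unbiased. This stands.
- **The tube is already in the screening column.** True. Footnote i and 6.5.1 nevertheless permit another time, and the consent heading still governs the row.

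**Conclusion.** The point holds in conditional form. The only HLA-A2 sample depends on a separate consent and may be drawn late, so 1-year survival by HLA-A2 may describe a selected subset and be too high in level. The late-draw route is the firmer of the two: its direction follows from counting survival from first dose, whereas the consent route needs an assumed link between willingness and prognosis.

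The size cannot be fixed from the protocol. Uptake of 60 to 90% with a gap of 10 to 20 points gives an overstatement of 1 to 8 points. A week-12 draw in 10 to 25% of patients gives about 1 to 2 points. All of these inputs are assumptions.

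It would be tempting to conclude that the HLA-A2 results will be self-selected, or that the comparison of HLA groups is biased. Neither follows. Uptake is unknown, and the comparison is distorted only if selection, through consent or early death, differs by HLA type. The primary endpoint, which uses all treated patients, is not affected.

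Separately, the standing of HLA-A2 is inconsistent: it is present in the synopsis and 9.5 and absent from 2.2 and 9.3.2.

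**What to change.** 1. Cover HLA-A2 typing from the planned 2 ml EDTA tube by the main study consent. Leave SNP analysis and stored serum, plasma and tissue under the separate consent.
2. Require the draw at screening or baseline by deleting the clause in footnote i of the schedule and in 6.5.1 that allows another time.
3. Align 2.2 and 9.3.2 with the synopsis and 9.5 on HLA-A2, and settle whether these subgroup results will or may be presented.
4. Report the number of untyped patients and their 1-year survival beside the two HLA groups.

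The cost is wording in the consent, schedule and objectives. No new tube is needed. The downside is small: HLA typing becomes part of the main consent, and a few more samples are typed.

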### 1.2.1 CTLA-4 and T Cell Activation

**Figure 1 Mechanism of Action**

[figure not shown]

Advances in the understanding of the mechanisms that regulate T cell activation have allowed the rational design of new strategies for immunotherapy of tumors, including melanoma. It has been known for some time that engagement of the T cell antigen receptor by itself is not sufficient for full T cell activation; a second co-stimulatory signal is required for induction of IL-2 production, proliferation and differentiation to effector function of naive T cells. Abundant data now indicate that the primary source of this costimulation is mediated by engagement of CD28 on the T cell surface by members of the B7 family on the antigen-presenting cell (APC) (Lenschow et al., 1996). (See Figure 1)

Expression of B7 has been shown to be limited to “professional” antigen presenting cells; that is, specialized cells of the hematopoietic lineage, including dendritic cells, activated macrophages, and activated B cells. It has been suggested that this sharply-defined restriction

of B7 expression is a fail-safe mechanism for maintenance of peripheral T cell tolerance, insuring that T cell activation can only be stimulated by appropriate APCs (Schwartz et al., 1992). The fact that tumor cells do not express B7 contributes to their poor capacity to elicit immune responses (Chen et al., 1992; Townsend et al., 1993).

The demonstration that induction of expression of B7 on many tumor cells by transfection, transduction, or other mechanisms can heighten tumor immunogenicity led to great interest in pursuing this as an approach to tumor immunotherapy. As demonstrated in vivo in murine tumor models, the utility of B7 expression as a vaccination approach is limited by the following factors: (1) B7-expressing tumor cell vaccines are only effective when the tumor cells have a high degree of inherent immunogenicity; (2) while B7-expressing vaccines have been shown in many cases to be effective in inducing protective immune responses, they have demonstrated only limited utility in inducing responses to established tumors; and (3) inactivation of tumor cells by radiation has been shown to destroy the immuno-enhancing activity of the B7 gene product (Townsend et al., 1994; Allison et al., 1995).

In the past few years it has become apparent that co-stimulation is even more complex than originally thought. After activation, T cells express CTLA-4, a close homologue to CD28. CTLA-4 binds members of the B7 family with a much higher affinity than CD28 (Linsley et al., 1991). Although there was initially some controversy as to the role of CTLA-4 in regulating T cell activation, it has become clear that CTLA-4 down-regulates T cell responses (Thompson & Allison, 1997). This was initially suggested by the following in vitro observations: (1) blockade of CTLA-4/B7 interactions with antibody enhanced T cell responses; (2) cross-linking of CTLA-4 with CD3 and CD28 inhibited T cell responses; and (3) administration of antibodies to CTLA-4 in vivo enhanced the immune response to peptide antigens or superantigens in mice (Walunas et al., 1994; Kearney et al., 1995; Krummel et al., 1995; 1996). Blocking CTLA-4-B7 interaction while preserving signaling via CD28 resulted in enhanced T cell responses in vitro (Kearney et al., 1995).

Perhaps the most convincing demonstration of the down-regulatory role of CTLA-4 came from examination of mice with a null mutation (Tivol et al., 1995; Waterhouse et al., 1995; Chambers et al., 1997). CTLA-4 knockout mice appear to have spontaneously activated T cells evident at approximately 1 week after birth, followed by rampant lymphoproliferation and lymphadenopathy. These mice die at approximately 3 weeks of age, either as a result of polyclonal T cell expansion and tissue destruction or as a result of toxic shock resulting from lymphokine production by the T cells. Since thymocyte differentiation and selection proceed normally in CTLA-4-deficient mice, the rampant T cell expansion that occurs in the mice indicates that CTLA-4 plays a critical role in down-regulating T cell responses in the periphery (Krummel et al., 1996).

